### Trial Design

The design of our pilot study is a prospective, single group, observational, prepost cross-over trial. Ethical approval was obtained from the Institutional Review Board at Stanford University (Protocol #32211). This study is registered at ClinicalTrials.gov (NCT02319434).

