### Objective

We hypothesize that using the Ostom-i alert sensor will result in an improved ostomy-specific, health-related quality of life as compared to baseline measurement before the use of the sensor. We intend to assess the change in ostomy-specific health-related quality of life, with the Ostom-i alert sensor. We will use the City of Hope Quality of Life Questionnaire for Patients with an Ostomy. Secondarily, we aim to measure the change in general health-related quality of life and ostomy adjustment using the Medical Outcomes Study 36-item short form health survey (SF-36) and the Olbrisch Ostomy Adjustment Scale Short Form 2 (OAS-SF2), respectively [15,16].

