#### Randomization

Patients will serve in both the control and interventional arms of this cross-over pilot study. A cross-over design is advantageous for this pilot study as it allows patients to serve as their own control, therefore variances attributable to confounding factors [18,19]. Once eligibility is confirmed, consent will be obtained and the baseline survey will be given (CoH-QOL-Ostomy, SF-36 and OAS-SF2). After completion of the baseline survey, the participant will be given their Ostom-i alert sensor along with a video tutorial which explains how to use the device.

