#### Intervention

Once completing the baseline survey, patients will enter the intervention arm of the study where they will receive an Ostom-i sensor which they will use over the course of 4 weeks. Two and 4 weeks after receiving the sensor, primary and secondary outcome measures will be assessed. The Ostom-i is a flexible, Bluetooth-linked sensor that attaches to the patient’s ostomy bag. The sensor portion of the Ostom-i device is a flexible potentiometer produced by Spectra Symbol [20]. The sensor determines the level of the ostomy bag based on the angle of flex it experiences and automatically adjusts when the user is laying down or standing up. The sensor can be adjusted in size from 7 cm to 9 cm to fit a variety of ostomy bag sizes. Data collected by the sensor is sent via Bluetooth to the user’s iOS or Android device and provides alerts informing the wearer of the level of their ostomy bag (Figure 1 and 2).

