#### Participant Timeline

Participants will retake all 3 surveys after 2 and 4 weeks of device use as previous validation studies of these surveys have used 2-4 week intervals [16,21]. Following completion of the week 4, survey participant involvement in the study will end (see Figure 3 for the study flowchart). Participants will have the option to take the week 2 and week 4 surveys either in person at the hospital or at home, using a paper-based or online format.

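### The study is labelled an observational cross-over with control and intervention arms, but it is a single-arm, fixed-order pre-post study that can show change from baseline, not an effect caused by the sensor

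*Protocol article*

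**What the plan says.** The Trial Design section gives four labels at once: "The design of our pilot study is a prospective, single group, observational, prepost cross-over trial". The Methods part of the Abstract also uses observational and cross-over.

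Under the heading Randomization, the article says: "Patients will serve in both the control and interventional arms of this cross-over pilot study". It presents this as a strength: "A cross-over design is advantageous for this pilot study as it allows patients to serve as their own control". The sentence ends with a clause on confounding that has lost its verb: "it allows patients to serve as their own control, therefore variances attributable to confounding factors".

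The procedures are given in three places:
- Randomization: "After completion of the baseline survey, the participant will be given their Ostom-i alert sensor along with a video tutorial".
- Intervention: "Once completing the baseline survey, patients will enter the intervention arm of the study where they will receive an Ostom-i sensor".
- Participant Timeline: "Participants will retake all 3 surveys after 2 and 4 weeks of device use". Participation ends after the week 4 survey.

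The Objective reads: "We hypothesize that using the Ostom-i alert sensor will result in an improved ostomy-specific, health-related quality of life as compared to baseline measurement". The last paragraph of the Discussion gives the purpose as finding out how far the sensor affects its users' quality of life. The Statistical Analysis section plans a paired t-test of pre- against post-intervention scores, with a mixed model or repeated-measures ANOVA as options.

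**The concern.** In a cross-over, each patient is observed under at least two conditions and the order varies between patients, so the effect of condition can be separated from the effect of period. Here the control arm is one questionnaire completed before the device is handed over. Everyone follows the same order, so time since baseline and sensor use coincide. The label observational does not fit either, because the study gives the patient the device.

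This goes beyond terminology, because the article argues from the label. It offers the cross-over as the reason the design is advantageous, and it words its hypothesis and purpose causally. A reader who accepts the label would take a significant paired test as evidence that the sensor improved quality of life. The design has no comparison that could support that conclusion.

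**Working it through.** **1. Label against procedure**

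| Feature implied by the labels | What the procedures describe |
|---|---|
| Two or more conditions, each observed over a period | One baseline survey, then 4 weeks on the sensor |
| Order varied between patients | One order for all: survey, sensor, survey at week 2, survey at week 4 |
| Randomised order (section heading) | No random allocation of any kind |
| Control arm | A single pre-sensor questionnaire |
| Observational | Sensor and video tutorial supplied by the study |

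**2. What the within-patient comparison removes**

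Write a patient's change as (sensor effect) + (everything else that changes between baseline and follow-up) + error. Stable patient characteristics cancel in the difference. The second term does not, and nothing in the data separates it from the first. The optional mixed model and repeated-measures ANOVA use the same single-sequence data and cannot separate them either.

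**3. Which sources of non-device change matter here**

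- *Expectation: strong.* Use is unblinded and the outcome is self-reported. Recruitment includes word of mouth, online advertisements and flyers, and participants keep a US $125 device (Recruitment).
- *Adjustment over time: weaker.* At least 6 months with an ostomy bag is required, and the article cites psychological adjustment at 6 to 10 weeks (Eligibility Criteria).
- *Regression to the mean: weaker.* No eligibility criterion selects on a low quality-of-life score.

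**4. The plan's own figure**

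Inputs from Null Hypothesis and Sample Size: SD 1.7, difference 15% of 8.0 = 1.2, 80% power, two-sided 5%.

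n = 1.7² × (0.842 + 1.960)² / 1.2² = 15.75, rounded up to 16, as stated. With 20% attrition, 16 / 0.8 = 20, as stated. The calculation is for a one-sample paired change, which is the design actually described, so the wrong label has not carried into the sample size.

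**5. Illustration of what could be misattributed**

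Assume no sensor effect and a mean rise b from other causes. The paired t-test then rejects with the noncentral-t probability for noncentrality b√n / 1.7 on n − 1 degrees of freedom (two-sided 5%):

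| Assumed rise b | Share of planned 1.2 | n = 16 | n = 20 |
|---|---|---|---|
| 0 | 0 | 5.0% | 5.0% |
| 0.4 | one third | 14.3% | 17.0% |
| 0.6 | one half | 26.2% | 32.3% |

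For example, b = 0.4 and n = 16 give a noncentrality of 0.4 × 4 / 1.7 = 0.94. The document gives no value for b, so these rises are assumptions. The SD is the plan's.

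**The case against.** The strongest defence is that the real design is disclosed. The labelling sentence itself says single group and pre-post, the order of events is plain, and the analysis is a paired pre-post comparison with no cross-over terms. The hypothesis and the null are worded against baseline, and a paired test answers that question. An uncontrolled pre-post study is also a legitimate choice for a 20-patient pilot.

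Much of this stands. The test and the sample size suit the design actually described, and no concurrent control is required for a pilot of this kind. What does not stand is the cross-over and control-arm wording, the advantage drawn from it, and the causal language of the Objective and Discussion.

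Three stronger readings are tempting, and the documents do not support them:

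- *That the test's 5% error rate is inflated to 14–32%.* The stated null is no improvement from baseline. If scores really rise by 0.4, that null is false and rejecting it is correct. The percentages measure the risk of misattribution when the result is interpreted.
- *That time drift and regression to the mean make an improvement likely without the sensor.* The 6-month criterion and the absence of selection on low scores make both weaker here. Expectation is the main threat.
- *That the own-control argument is simply false.* Within-patient comparison does remove stable differences between patients. The sentence on confounding is incomplete, so exactly how much it claims cannot be read.

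**Conclusion.** The point holds as an error in how the design is described and in what it is said to show. The document calls the study an observational cross-over with control and interventional arms. Its procedures describe a single-arm, fixed-order, pre-post study of a supplied device whose only control is one baseline questionnaire. It can estimate change from baseline during sensor use, but it cannot attribute that change to the sensor.

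This conclusion rests on the text alone and needs no assumed number. The illustrative chances of misattribution (about 14–17% for a 0.4-point rise, about 26–32% for 0.6) depend on the assumed rises, the plan's SD of 1.7 and 16 to 20 completers. The sample size arithmetic and the choice of a paired test are not at fault on this point.

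**What to change.** **Needed (wording only):**

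1. In the Abstract (Methods), Randomization and Trial Design, replace the terms cross-over, control arm and observational with *single-arm, pre-post interventional pilot*. Rename the Randomization section accordingly.
2. Complete the sentence on confounding, and limit the own-control argument to stable differences between patients.
3. In the Abstract (Objective), the Objective section and the last paragraph of the Discussion, state the aim as change from baseline in ostomy-specific quality of life during sensor use. Word the eventual conclusion the same way, and name expectation as the main alternative explanation.

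This costs an amendment to the text, with no change to visits, sample size or analysis.

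**Optional:** add a second pre-sensor survey two weeks before hand-over, and report the change without the sensor beside the first two-week change with it. This would give an estimate of drift and repeat-survey effects. It requires earlier consent, lengthens participation by two weeks and adds some attrition risk. It would not remove expectation bias or the fixed order, so the wording changes would still be needed.

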### Data Collection, Management, and Analysis

#### Primary Outcome Data Collection Methods

Our primary outcome, change in ostomy-specific, health-related quality of life from baseline, will be measured using the modified CoH-QOL-Ostomy. This survey was designed and studied for reliability and validity by Grant et al [14] with an overall questionnaire alpha of .95, suggesting strong consistency. The survey can be divided into 6 sections: 1) social adjustment to ostomy (coefficient alpha=.90, correlation to single quality of life item: *r*=.44, *P*>.001); 2) general quality of psychological well-being (coefficient alpha=.83, correlation to single quality of life item: *r*=.76, *P*>.001); 3) general quality of physical well-being (coefficient alpha=.88, correlation to single quality of life item: *r*=.39, *P*>.001); 4) disease-specific effects on physical well-being (coefficient alpha=.77, correlation to single quality of life item: *r*=.24, *P*>.001); 5) general quality of spiritual well-being (coefficient alpha=.81, correlation to single quality of life item: *r*=.51, *P*>.001); and 6) disease specific effects on psychological well-being (coefficient alpha=.82, correlation to single quality of life item: *r*=.38, *P*>.001) [14]. This validated survey has successfully been used by number of studies examining ostomy-related quality of life [22-27].

#### Secondary Outcome Data Collection Methods

Our secondary outcomes, general health-related quality of life and psychological adjustment to the ostomy, will be measured using the SF-36 and the OAS-SF2. The SF-36 involves a scale which measures 8 health profiles including physical functioning (PF), role limitations due to physical health problems (RP), bodily pain (BP), general health perceptions (GH), vitality (VT), social functioning (SF), role limitations due to emotional problems (RE), and mental health (MH). The SF-36 also yields physical and mental health summary measures and is scored using a Likert scale [28]. Furthermore, the SF-36 has been validated and was found to be reliable across a diverse group of patients with various physical and psychological issues [28,29]. Each of the 8 dimensions of the SF-36 have been found to have a Cronbach alpha statistic greater than the minimum standard of .70; PF (alpha=.90), SF (alpha=.76), RP (alpha=.88), RE alpha=.80), MH (alpha=.83), VT (alpha=.85), GH (alpha=.78), and BP (alpha=.82) suggesting strong internal-consistency and reliability [28,30,31].

Adjustment to ostomy will be evaluated using OAS-SF2 [16]. The OAS is a subjective scale specific to persons with an ostomy, and examines social, psychological, and sexual functioning adjustment to living with an ostomy. The OAS is measured on a 6-point Likert scale and contains 34 items. Cronbach’s alpha for the scale was calculated at alpha=.85 with a test-retest reliability at *r*=.72 and later confirmed in studies of Swedish, Norwegian, and Chinese patients with an ostomy [32-34]. Two, 17-question short forms (short form 1 and short form 2) were created by Olbrisch based on the original 34 questions. It was determined that each short form could be used independently without compromising reliability or validity of the 34-question-long form (*r*=.96). Furthermore, short form test-retest consistency and reliability was determined to be *r*=.69 [21].

#### Data Management

Survey assessments will be collected via Stanford Qualtrics (Qualtrics, Provo, UT) survey or pen-and-paper [17]. Data will be entered into the Stanford Research Electronic Data Capture (REDCap) databases (Vanderbilt, Nashville, TN) [35]. All data will be entered and de-identified by trained staff and undergo data quality and accuracy checks.

#### Statistical Analysis

Data will be presented as mean (SD). Changes between pre- and postintervention quality of life will be assessed using a dependent participant’s paired *t*-test with 95% confidence interval. Depending on participant retention throughout the course of the study, we may choose to use mixed model regression analysis which would allow us to incorporate incomplete data sets from participants who might not complete the study. Furthermore, we also may choose to use repeated measures analysis of variance to examine differences in population mean scores over the 3 study sessions.

### Monitoring

#### Data Monitoring

A data monitoring committee (DMC) will not be used in this study. In accordance with the United States Food and Drug Administration Title 21 (21 Code of Federal Regulation 812) and the Stanford University Institutional Review Board (IRB), the Ostom-i alert sensor was not deemed to pose a significant risk to study participants [36]. Furthermore, there is an overall low level of concern for patient safety with the Ostom-i alert sensor. Given the short timeframe of the study, a DMC may not be practical and it is not likely that a DMC will aid in improving the scientific validity of this study [37]. This study is in full compliance with the guidelines outlined by ClinicalTrials.gov.

#### Risk and Side Effects

Due to the minimal intervention in this study, participants are at very low risk for adverse events. Should any adverse events occur, they will be systematically logged and reported to ClinicalTrials.gov. Adverse events involving the ostomy site or the ostomy bag, which are not related to the Ostom-i alert sensor, will be directed to the study participant’s gastroenterologist.

#### Auditing

This study is being conducted independently from the Ostom-i alert sensor parent company, 11 Health and Technologies, LLC. 11 Health and Technologies, LLC will not audit any aspect of the study. Due to the short duration of this study (12 months), auditing is not deemed a necessary component of our protocol.

### Ethics and Dissemination

#### Research Ethics Approval and Protocol Amendments

Ethical approval was obtained from the IRB at Stanford University (Protocol #32211). Any amendments made to the study protocol will be immediately reported to the IRB at Stanford University as well as to ClinicalTrials.gov.

#### Consent or Assent and Confidentiality

Informed consent will be obtained from study participants by study research personnel prior to in-person baseline evaluation. Phone conversations and in-person visits will take place in a private room to protect patient privacy. Data collected by the Ostom-i alert sensor will remain on the participant’s personal device (iPhone, Android, tablet etc) for the duration of the study. Meetings and phone calls will not be recorded and will only involve necessary study staff. 

Data collected from participants will include demographic information such as names, telephone numbers, addresses, birthdates, email addresses, illness/diagnosis, gender, age, height, weight, ethnicity, marital status, records of waste output as measured by the Ostom-i alert sensor as well as results from the CoH-QOL-Ostomy, SF-36, and Olbrisch’s Ostomy Adjustment Scale. Demographic and survey data will be collected and stored in a secure database on an encrypted computer. 

Participants will be assigned a random, 2-digit numerical identifier which will be stored in a locked safe in the laboratory. Collected data will also be stored in the secure REDCap database and necessary data transfer will occur using secure methods (eg, emails marked as secure). All aspects of data security in this study are in full compliance with the Stanford University Office of Audit, Compliance, Risk and Privacy.

#### Access to Data

Final trial data will only be available to study research personnel. All necessary demographic and results data will be uploaded to ClinicalTrials.gov in accordance with their rules and regulations.

#### Ancillary and Posttrial Care

Should study staff identify health issues in participants over the course of the study, they will be immediately referred to their primary care physician or gastroenterologist. Furthermore, study physicians will be available to answer study participant questions. No poststudy follow-up of participants will occur.

#### Dissemination Policy

The study authors plan to publish collected data in a peer-reviewed journal (to be determined at a later date). Furthermore, this study is fully compliant with the guidelines set forth by ClinicalTrials.gov and as such all necessary information will be made available in a timely manner. All listed authors and/or contributors are compliant with guidelines outlined by the International Committee of Medical Journal Editors for author inclusion in a published work. Public access to the study protocol and other necessary aspects will be made available through our ClinicalTrials.gov identifier (NCT02319434).

## Discussion

The Ostom-i alert sensor is a novel, wearable sensor that allows for easier output measurements and anticipation of ostomy bag changes via Bluetooth connection to a mobile phone. The Ostom-i alert sensor has the potential to improve quality of life of users by giving them freedom and confidence to partake in daily activities with the knowledge that they can check how full their ostomy bag is in a private, discrete manner. To examine the extent to which the Ostom-i alert sensor affects quality of life, 20 participants will be recruited to wear the Ostom-i alert sensor for 1 month. Health-related quality of life will be determined by using the CoH-QOL-Ostomy. This survey will be given at baseline to individuals who have had an ostomy bag for 6 months or longer, then again 2 and 4 weeks after beginning with the Ostom-i sensor. Ultimately, we anticipate that the Ostom-i alert sensor may improve health-related quality of life as measured by the CoH-QOL-Ostomy.

Proposed benefits of mHealth technologies, such as the Ostom-i, include a reduction in the cost of care by lowering resource utilization and infection rates, improving patient-provider communication, and reducing time spent as an inpatient [38-40].

A number of mHealth technologies, such as the Ostom-i alert sensor have recently been released including devices, such as the Withings Blood Pressure Monitor, the Sanofi iBGStar Blood Glucose Meter, and the AliveCor Mobile ECG. While these devices have all been validated in the peer-reviewed literature, few studies have examined to what extent, if any, they reduce burden on health care systems [41-43]. 

A 2006 study by Leijdekkers and Gay [44] analyzed a novel, cell phone–linked heart monitor and suggest that by visualizing their personal cardiac data in real time, users are less likely to visit the hospital, which in turn reduces hospital staff workload, reduces costs of patient-provider communication, and improves patient self-care [44]. Free et al [45] examined the literature and found 42 controlled trials of mobile technology–based systems aimed at improving health care service delivery [45]. They report only a modest benefit towards clinical management and diagnosis with the use of mobile technologies. 

Bloss et al [46] examined the extent to which the Withings Blood Pressure Monitor, the Sanofi iBGStar Blood Glucose Monitor, and the AliveCor Mobile ECG affected health care resource utilization measured by both health insurance claims and hospital visits. In their study, participants were split into control and intervention arms where those in the intervention arms utilized one of the 3 aforementioned technologies based on their health care needs. No difference between groups was observed for office visits (*P*=.46), inpatient stay (*P*=.82), emergency room visits (*P*=.06), or pharmacy claims (*P*=.60). Furthermore, no difference in self-efficacy change was observed between control and intervention group (*P*=0.85), and no difference in filed insurance claims between the 2 groups was observed (*P*=0.62) [46].

While future studies may examine whether mHealth technologies, such as the Ostom-i alert sensor, influence cost of care or duration of hospital stay, the purpose of the present study is to examine the extent to which the Ostom-i alert sensor affects the health-related quality of life of its users. To our knowledge, no such studies have been conducted, making this a unique undertaking.

